**Sample size calculation**

A recent Kenyan study placed failed induction at 26%.

We postulate that offering a combined use of misoprostol and Foley catheter will reduce this proportion to 16%.

Therefore for us to detect a 16% difference in the successful induction following the use of Foley with misoprostol versus misoprostol alone, we estimated using the sample size formula,

Sample size formula

[Allan Donner; Stat. Medicine (1984)

that we would need to study a total of 180 women (90 per group) to achieve a 80% power to detect the stated difference of 16% at a two-sided alpha=0.05 level of significance.

Where we define p_c_=74% and p_a_=90% to be the proportions of women in the misoprostol and combined misoprostol and Foley groups respectively

and = (p_C_ + p_a_)/2 ( =1.960, and =0.84

**Data collection, management and analysis**.

Data collection and storage: Data will be collected by use of questionnaires by the principal investigator and 3 or 4 well trained research assistants. Information will be obtained from history, review of medical records and clinical examination. The information will be stored safely in a password-protected computer and backed up on a dedicated USB drive. Any hard copy records carried for analysis will be stored under lock and key and patients confidentiality will be observed. A qualified statistician will do analysis as per protocol with intent to treat analysis using SPSS version 21.Primary outcome will be failed induction/successful induction and secondary outcomes include time to delivery, maternal and perinatal outcomes. Proportions will be compares using Chi2 test, 95% CI, two tailed hypothesis with p significant at <0.05

Ethical considerations.

- Permission will be sought from the KNH/UON ERC.
- Informed Consent.
- Confidentiality.
- Patients who decline to give consent will be treated as per the existing protocols and no penalty at all.

Study limitations

Non-blinding may have influence patient management

No long-term follow up of mother and neonate for late outcomes

No interim analysis due to resources.

Study timelines

- Proposal presentation-January 2014
- ERC approval and registration-February 2015
- Enrollment-march-September 2015
- Analysis-September-December 2015
- Presentation-December 2015
- Publishing-December-June 2016
- Dissemination of results-June 2016

Study budget

The anticipated expenses during this study include the following-

Buying of Foleys catheters and misoprostol-

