7-The combination of balloon catheter plus oxytocin is recommended as an alternative method of induction of labor when prostaglandins (including misoprostol) are not available or are contraindicated.

8-In the third trimester, in women with a dead or an anomalous fetus, oral or vaginal misoprostol are recommended for induction of labor.

9- Sweeping membranes are recommended for reducing formal induction of labor.

MANAGEMENT OF ADVERSE EFFECTS ASSOCIATED WITH INDUCTION OF LABOUR

Betamimetics are recommended for women with uterine hyper- stimulation during induction of labor. Uterine hyper stimulation is defined as either occurrence of uterine contractions lasting more than 60 seconds, or occurrence of more than four contractions within 10 minutes, regardless the state of the fetus.Terbutaline is the main beta mimetic used.Tocolytics like magnesium sulfate,atosiban and nitroglycerin have a small effect(3).

Setting for induction of labor

Outpatient induction of labor is not recommended for improving birth outcomes. This because induction of labor requires facilities for monitoring maternal and fetal well-being. Secondly induction should be done in a facility which has the capacity of doing a cesarean section(3).

**DEFINITION OF FAILED INDUCTION**.

Failed induction is defined as labor not starting after one cycle of treatment or after 24 hours. If induction fails, healthcare professionals should discuss this with the woman and provide support. The woman’s condition and the pregnancy in general should be fully reassessed, and fetal wellbeing should be assessed using electronic fetal monitoring. If induction fails, decisions about further management should be made in accordance with the woman’s wishes, and should take into account the clinical circumstances. The subsequent management options include: a further attempt to induce labor (the timing should depend on the clinical situation and the woman’s wishes) or caesarean section.(7). A study done by Osaheni Lucky et al. (Nigeria, 2014) found out 24.1% rate of failed induction. Locally, a study done by Esiromo (KNH, 2011) found out 26% rates of failed induction. The study also found out 77.7% success rate with misoprostol alone and 40% success with Foleys catheter alone.

**Predictors of successful induction of labor**.

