**Control arm**

Misoprostol alone

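### The 74% success rate planned for misoprostol alone conflicts with the 77.7% the protocol reports for that treatment; at 77.7% against 90%, power is about 61%, not 80%

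*Protocol*

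**What the plan says.** The control arm is "Misoprostol alone" (Protocol, Control arm).

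The section Sample size calculation begins with "A recent Kenyan study placed failed induction at 26" per cent. The planning values follow: "Where we define p_c_=74% and p_a_=90% to be the proportions of women in the misoprostol". The second of these, 90%, is for the combination arm. The resulting size is 90 women in each arm, 180 in all, and the stated aim is "to achieve a 80% power to detect the stated difference of 16% at a two-sided alpha=0.05 level of significance".

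The definition of failed induction in the Introduction describes a local study at the trial hospital (2011) that "found out 26% rates of failed induction", with no method named. The next sentence reads: "The study also found out 77.7% success rate with misoprostol alone and 40% success with Foleys catheter alone".

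The sample size section also says that failure is expected to fall to 16% with the combination. That is 84% success, not the 90% used in the calculation.

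**The concern.** For the treatment in the control arm, the protocol reports one success rate (77.7%) and sizes the trial on another (74%). Both appear to come from the same study. If success is the complement of failure, 26% failure and 77.7% success cannot both describe misoprostol alone, because 77.7% success leaves 22.3% failure.

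The most natural explanation is that 26% is a rate across induction methods, pulled down by the 40% success with Foley alone.

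A control success rate that is 3.7 points too low (77.7 − 74) widens the assumed gap to a fixed 90% target by the same amount. The trial would then be less sensitive than stated, and a non-significant result could be read as absence of benefit. The protocol states no allowance for drop-out, describes no re-estimation of the sample size and rules out an interim analysis, so nothing later in the plan would reveal or correct a shortfall.

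**Working it through.** **Inputs**
- Planned success 74% (misoprostol) and 90% (combination), 90 per group, two-sided 0.05, 80% power: Sample size calculation.
- Success with misoprostol alone 77.7%, with Foley alone 40%: definition of failed induction, Introduction.
- Failure on the combination 16%, i.e. 84% success: Sample size calculation.
- Chi-squared test: Data collection, management and analysis. Allocation 1:1: Methodology.

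**Formula** (normal approximation, pooled variance under the null, no continuity correction). With d the difference, p̄ the mean of the two proportions, s0 = √[2p̄(1−p̄)] and s1 = √[p1(1−p1) + p2(1−p2)]:
- power = Φ[(d√n − 1.96·s0)/s1]
- n per group = (1.96·s0 + 0.84·s1)²/d²

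**Step 1. Reproduce the plan (74% vs 90%).** d = 0.16, p̄ = 0.82, s0 = 0.5433, s1 = 0.5314.
- n = (1.0649 + 0.4464)²/0.0256 = 89.2, so 90 per group.
- Power at 90: (0.16 × 9.4868 − 1.0649)/0.5314 = 0.852, Φ = 80.3%.

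The stated sample size is arithmetically correct for its inputs.

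**Step 2. Change only the control rate (77.7% vs 90%).** d = 0.123, p̄ = 0.8385, s0 = 0.5204, s1 = 0.5131.
- Power at 90: (1.1669 − 1.0200)/0.5131 = 0.286, Φ = 61.3%.
- n for 80% power: (1.0200 + 0.4310)²/0.015129 = 139.2, so 140 per group.
- Exact enumeration of the uncorrected chi-squared test gives 61.8%; the unpooled approximation gives 62.3%.

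**Step 3. Other readings of the target, control 77.7%, 90 per group**

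| Combination success | Basis | d | s0 | s1 | z | Power |
|---|---|---|---|---|---|---|
| 93.7% | 16-point difference kept | 0.160 | 0.4951 | 0.4820 | 1.136 | 87.2% |
| 92.5% | value that gives 80% power | 0.148 | 0.5036 | 0.4926 | 0.847 | 80.1% |
| 90% | the planned combination rate | 0.123 | 0.5204 | 0.5131 | 0.286 | 61.3% |
| 84% | failure falls to 16% | 0.063 | 0.5565 | 0.5547 | −0.889 | 18.7% |

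**Step 4. Could 74% be a pooled rate?** Assuming that the source used only these two methods, w × 77.7 + (1 − w) × 40 = 74 gives w = 34/37.7 = 0.90. A mix of about 90% misoprostol and 10% Foley is possible. Some weight would reproduce any value between 40% and 77.7%, so this shows compatibility and nothing more.

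**The case against.** **The power loss depends on what is held fixed.** The protocol claims 80% power for a 16-point difference. Keeping that difference at a 77.7% control rate raises power to about 87%. This stands as a limit on the 61%. However, it needs 93.7% success in the combination arm, a value stated nowhere in the protocol, whereas 90% is the stated planning value.

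**The 90% is itself contradicted.** The same section has failure falling to 16%. That conflict is separate and larger: 74% against 84% gives about 38% power at 90 per group. This stands too. The 61% rests on an input that the protocol has not reconciled, and resolving the target alone would still leave the control rate unexplained.

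**The source is not visible.** A reader might infer that 26% is the source study's overall rate and that the wrong line of its results was used. The protocol does not call the 26% overall or pooled, and the sample size section does not name its Kenyan study. The matching 26%, the local setting and the separate rates by method make the inference probable, but do not prove it.

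**Success and failure may not be complements.** The Abstract ties success to vaginal birth and failure to not passing 3 cm of dilatation after 24 hours. A woman could meet neither. If the source worked this way, 77.7% success does not imply 22.3% failure. The protocol does treat the two as complements when it turns 26% into 74%, so it should apply that consistently or explain why not.

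**The gap may be within sampling error.** The source's size is not given. If its misoprostol group had fewer than about 485 women, a 95% interval around 77.7% would reach 74% (1.96 × √(0.777 × 0.223/485) = 0.037). So 74% may be defensible as a cautious planning value, but the protocol offers no such argument.

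**Conclusion.** The concern holds as an unexplained conflict between two planning figures in one document, not as an arithmetic error: 90 per group is correct for 74% against 90%.

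With the protocol's own rate for misoprostol alone and its own 90% for the combination, power is about 61%, so the type II error is about 39% instead of 20%. At 90 per group, 80% power holds only for about 92.5% success on the combination. Across the targets that the section allows, power runs from about 19% to about 87%.

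These figures assume that 77.7% is the right expectation for the control arm, that success and failure are complements, that the test is the uncorrected chi-squared and that no women are lost.

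Two stronger readings are not supported. It cannot be said that the trial lacks 80% power whatever the target, because a preserved 16-point difference would give more. Nor can it be stated as fact that 26% is a pooled rate taken in error.

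**What to change.** In Sample size calculation:
1. Base the control rate on the misoprostol-alone figure of 77.7% and cite the study it comes from.
2. Reconcile the 16% failure and 90% success targets, so that one combination rate and one difference are stated.
3. Restate the power for 90 per group: about 61% for 90% success, and 80% only for about 92.5% success (failure from 22.3% to 7.5%).
4. If 74% is kept, say why it is expected with misoprostol alone, say whether the 26% covers several methods and whether success and failure are complements, and report the power at 77.7% beside it.

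The cost is protocol wording. The trial need not be enlarged for this; the 140 per group shows the size of the shortfall. The stated power, or the difference that the trial can detect, becomes less favourable.

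### The sample-size section gives two incompatible design effects for failed induction (26% to 16%, and 26% to 10%); the 90 per group and 80% power belong only to the second

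*Protocol*

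**What the plan says.** All of the relevant text is in the protocol's section on sample size calculation.

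- The control rate: "A recent Kenyan study placed failed induction at 26" per cent.
- The expected rate with the combination: "We postulate that offering a combined use of misoprostol and Foley catheter will reduce this proportion to 16" per cent.
- The difference used for sizing, in the next sentence: "Therefore for us to detect a 16% difference in the successful induction following the use of Foley with misoprostol versus misoprostol alone".
- The size and power: "that we would need to study a total of 180 women (90 per group) to achieve a 80% power", and this is "to detect the stated difference of 16% at a two-sided alpha=0.05 level of significance".
- The formula inputs: "Where we define p_c_=74% and p_a_=90% to be the proportions of women in the misoprostol and combined misoprostol and Foley groups respectively".

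The same section plans a two-tailed chi-square test at 0.05. The methodology section sets 1:1 allocation, and the outcomes section names failed induction as the primary outcome.

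**The concern.** The second statement sets a target rate for failure. The third and fifth set a difference and a pair of success rates. They describe different effects:

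| Statement | Failure, misoprostol alone | Failure, combination | Success | Difference |
| --- | --- | --- | --- | --- |
| Expected rate | 26% | 16% | 74% vs 84% | 10 points |
| Difference and formula inputs | 26% | 10% | 74% vs 90% | 16 points |

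The sizing sentence is introduced as following from the expected rate, but it does not follow from it. The number 16 appears as a rate in one sentence and as a difference in the next.

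This is the only power statement in the protocol and it concerns the primary outcome. Someone who takes the expected rate at face value, such as an ethics committee or a later reader of the results, would think that 180 women give 80% power to show a fall to 16%. The limitations state that there will be no interim analysis, so no planned look at the data would expose a mismatch. The hypothesis is framed as no difference in failed induction, so a non-significant result could be read as support for it even if the trial had little chance of detecting the effect its authors expected.

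**Working it through.** **Inputs.** All come from the sample-size section, except the 1:1 ratio, which is in the methodology section. Control failure 26% (success 74%); combination failure either 16% (expected rate) or 10% (formula inputs, success 90%); z-values 1.960 and 0.84; 90 per group.

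**Formula.** The formula itself is incomplete in the text available, but its ingredients are given: the two proportions, their mean and the two z-values. They fit the usual comparison of two proportions without continuity correction. With q = 1 − p, p̄ the mean of the two proportions and d their difference,

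n per group = [1.96 × √(2p̄(1 − p̄)) + 0.84 × √(p₁q₁ + p₂q₂)]² / d².

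Failure and success proportions give the same n.

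**Step 1: reproduce the stated size (success 74% vs 90%).**
- p̄ = 0.82; 2p̄(1 − p̄) = 0.2952; square root 0.5433; × 1.96 = 1.0649.
- p₁q₁ + p₂q₂ = 0.1924 + 0.0900 = 0.2824; square root 0.5314; × 0.84 = 0.4464.
- Sum 1.5113; squared 2.2840; divided by 0.16² = 0.0256 gives **89.2, so 90 per group**.

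This matches the protocol.

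**Step 2: power at 90 per group for that effect.** Power = Φ{[d√n − 1.96√(2p̄(1 − p̄))] / √(p₁q₁ + p₂q₂)}.
- d√n = 0.16 × 9.4868 = 1.5179; (1.5179 − 1.0649) / 0.5314 = 0.852; Φ(0.852) = **80.3%**.
- Exact binomial enumeration of the uncorrected Pearson chi-square test gives 81.2%.

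**Step 3: the same size at the expected rate (failure 26% vs 16%).**
- p̄ = 0.21; 2p̄(1 − p̄) = 0.3318; square root 0.5760; × 1.96 = 1.1290.
- p₁q₁ + p₂q₂ = 0.1924 + 0.1344 = 0.3268; square root 0.5717.
- d√n = 0.10 × 9.4868 = 0.9487; (0.9487 − 1.1290) / 0.5717 = −0.315; Φ(−0.315) = **37.6%**.
- Exact binomial enumeration of the same chi-square test gives 37.5%, or 31.3% with continuity correction. Even a one-sided test would have only 50.1% by the formula.

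**Step 4: size for 80% power at 26% vs 16%.**
- 0.84 × 0.5717 = 0.4802; sum 1.1290 + 0.4802 = 1.6092; squared 2.5895; divided by 0.01 gives 259.0.
- With the less rounded z-value 0.8416 it is 259.2, so **about 260 per group, 520 in total**. With continuity correction it is 279 per group.

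**Step 5: what 90 per group can detect.** Steps 1 and 2 show that power reaches 80% when the combination rate is about 10%. That is the largest failure rate below 26% that 90 per group can detect with 80% power. Lower rates are easier to detect (8% gives about 90% power by the Step 2 formula); higher ones, including 16%, are harder.

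The protocol states no allowance for dropout, so none is applied.

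**The case against.** The strongest reply is that the calculation is correct and only one sentence is off. The 16-point difference is stated twice, and the pair 74% and 90% is explicit; a single clause points the other way. If its *to* was a slip for *by*, or its 16 a slip for 10, everything else agrees, 180 women stand and the trial has the power it claims. This is a plausible reading, perhaps the likelier one, and the protocol offers nothing that excludes it.

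It follows that two stronger inferences are not supported. A reader might infer that the protocol claims 80% power for a fall to 16% and is therefore wrong about its power. It does not: the 80% is attached to the 16-point difference, and for that it is right. A reader might also infer that the trial is too small and should recruit about 520 women. That would follow only if 16% is the intended target and 80% power for it is required; the protocol establishes neither.

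What the reply does not remove is the contradiction. The sentence stating the expected effect on the primary outcome is incompatible with the effect used to size the trial. The cause can be guessed, but the text does not state it. Only the sponsor can say which target was meant.

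**Conclusion.** The point holds as an internal contradiction in the design effect, with a conditional consequence for power. The stated size and power are right for failure falling from 26% to 10%. They do not apply to a fall to 16%, for which 90 per group has about 38% power. A true effect of that size would then be missed about 62% of the time (100 − 38).

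These figures assume a true control rate of 26%, equal groups of 90 with complete outcome data, and a two-sided uncorrected chi-square test at 0.05. The conclusion does not depend on the choice of approximation: across the two-sided calculations, power at 26% versus 16% lies between about 31% and 38%.

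Because this is the protocol's only justification of sample size, the passage should be corrected whichever target was intended.

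**What to change.** State which target was meant, then make the sentence, the proportions and the power statement agree.

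- **If failure falling from 26% to 10% was meant:** replace *to 16%* with *by 16 percentage points, to 10%*, and say that the 80% power of 180 women applies to that effect only. The sample size does not change.
- **If failure falling to 16% was meant:** correct the difference to 10 points and the success proportions to 74% and 84%, and restate the power of 180 women as about 38%.

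Either change is to wording alone and needs no extra participants. The cost falls under the second reading: the stated power drops from 80% to about 38%, and the protocol would have to acknowledge that the trial is more likely than not to miss the effect it expects. Restoring 80% power for that effect would take about 260 per group, which goes beyond a wording change and is for the sponsor to decide.

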2. Induction of labor is not recommended in women with an uncomplicated pregnancy at gestational age less than 41 weeks.
3. If gestational diabetes is the only abnormality, induction of labor before 41 weeks of gestation is not recommended.
4. Induction of labor at term is not recommended for suspected fetal macrosomia.
5. Induction of labor is recommended for women with prelabour rupture of membranes at term.
6. For induction of labor in women with an uncomplicated twin pregnancy at or near term, no recommendation was made as there was insufficient evidence to issue a recommendation. If prostaglandins are not available, intravenous oxytocin alone should be used for induction of labor. Amniotomy alone is not recommended for induction of labor.

Methods of induction of labor

Methods of labor induction include mechanical and pharmacological means. Optimal choice of these depends on the pre-induction status of the cervix. The three factors most likely to lead to success include favorable cervix, multiparity and prior vaginal delivery. The cervix is considered unfavorable if the bishop score is less than 6.The most important element of bishop score is dilation, followed by effacement, station and position, with the least useful element being cervical consistency. Xenakis et al clearly demonstrated that women who had a bishop score of 3 or less at onset of induction had significantly higher rates of failed induction and caesarean delivery then those with a bishop score above 3.

Table 1-Bishop scoring system.

| Factor | 0 | 1 | 2 | 3 |
| --- | --- | --- | --- | --- |
| Dilatation (cm) | 0 | 1-2 | 3-4 | >5 |
| Effacement (%) | 0-30 | 40-50 | 60-70 | >80 |
| Consistency | Firm | Medium | Soft |  |
| Position | Posterior | Central | Anterior |  |
| Station | -3 | -2 | -1 or 0 | +1 or lower |

WHO has proposed the following recommendations,

1-If prostaglandins are not available, intravenous oxytocin alone should be used for induction of labor. Amniotomy alone is not recommended for induction of labor.

2- Oral misoprostol (25 μg, 2-hourly) is recommended for induction of labor.

3- Low-dose vaginal misoprostol (25 μg, 6-hourly) is recommended for induction of labor.

4- Misoprostol is not recommended for induction of labor in women with previous caesarean section.

5- Low doses of vaginal prostaglandins are recommended for induction of labor.

6-Balloon catheter is recommended for induction of labor.

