Successful induction of labor is more likely if there is a good Bishop score, more than 3,multiparity and Prior vaginal delivery. Xenakis et.al clearly demonstrated that women who had a bishop score of 3 or less at onset of induction had significantly higher rates of failed induction and caesarean delivery then those with a bishop score above 3.

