**Secondary outcome**

Induction to delivery time

Mode of delivery

Maternal outcomes-PPH, chorioamnionitis,hyperstimulation(5 contractions in 5mins)

Perinatal outcomes (APGAR, NICU admission

Methodology

Block randomization of all eligible consenting subjects by computer generated random sequences and a randomization ratio of 1:1.Upon enrollment, an opaque envelope containing the participant’s enrollment number and assignment to either the Foley plus vaginal misoprostol or vaginal misoprostol alone will be opened .Each participant will be assigned a unique 4-digit-long subject number for subject identity and confidentiality. Participants and health provider will be aware of the treatment allocation at the time of assignment of treatment.

Study procedures.

Patients who fall in the Misoprostol arm will be given 25 mcg vaginally 6hourly up to a maximum of 4 doses, Bishop score >6 or when they go into active labor. Later amniotomy and augmentation may be done as per protocol

Patients who fall in the Combination arm will be inserted an 18-French Foley catheter with a 30 cc balloon will be placed just above the internal cervical os and then inflated with 30 cc of sterile saline. The length of the Foley catheter will be affixed to the subject’s inner thigh under slight tension. At the same time 25 mcg of misoprostol is inserted at the posterior fornix of the vagina 6 hourly up to a maximum of 4 doses, Bishop score >6 or active labor. If difficult, Foley catheter insertion will be attempted every 6 hours unless Bishop score more than 6 or in active labor. When Foley balloon falls off, labor may be augmented or amniotomy performed as per the existing protocol.

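### Using parity and baseline Bishop score in the primary analysis would be a cheap, modest improvement on the unadjusted Chi2 test, which is itself valid

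*Protocol*

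**What the plan says.** **Analysis.** Under *Data collection, management and analysis*, the protocol plans an intention-to-treat analysis with failed or successful induction as primary outcome. The method is: "Proportions will be compares using Chi2 test, 95% CI, two tailed hypothesis with p significant at <0.05". No covariate or stratified comparison is mentioned.

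**Randomisation.** The *Methodology* text under *Secondary outcome* says: "Block randomization of all eligible consenting subjects by computer generated random sequences and a randomization ratio of 1:1". No stratification factor is named.

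**Predictors.** *Methods of induction of labor* states: "The three factors most likely to lead to success include favorable cervix, multiparity and prior vaginal delivery". It also reports from a cited study that "women who had a bishop score of 3 or less at onset of induction had significantly higher rates of failed induction". *Predictors of successful induction of labor* repeats this, naming a Bishop score above 3, multiparity and prior vaginal delivery.

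**Availability at baseline.** The inclusion criteria set an upper limit on the Bishop score, and the exclusion criteria set one on parity. Both must therefore be assessed before randomisation. The protocol does not list the variables on the questionnaire.

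**Sample size.** The formula uses success proportions of 74% and 90%, with 90 women per group, "to achieve a 80% power to detect the stated difference of 16% at a two-sided alpha=0.05 level of significance".

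**The concern.** The protocol identifies factors that it believes govern the primary outcome, and must assess two of them before allocation, but uses neither in the design or in the stated comparison. Two things follow.

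1. If the factors are prognostic, a comparison within strata removes outcome variation that the crude comparison treats as noise. The planned power is just over 80%, so even a small gain is useful.
2. Only one trial will be run. If, by chance, more nulliparous women or more women with low Bishop scores fall in one arm, the crude difference carries that imbalance. Deciding to adjust after seeing it would be data-driven, so the choice has to be made in advance.

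**Working it through.** **1. The plan's own figure.** Inputs from *Sample size calculation*: success 74% and 90%, two-sided alpha 0.05 (z = 1.96), power 80% (z = 0.84). The mean proportion is (0.74 + 0.90)/2 = 0.82.

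n per group = [1.96 × √(2 × 0.82 × 0.18) + 0.84 × √(0.74 × 0.26 + 0.90 × 0.10)]² / 0.16²
= [1.065 + 0.446]² / 0.0256 = 89.2, rounded up to 90.

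Power at 90 per group: z = (0.16 × √90 − 1.065) / 0.531 = 0.852, which gives 80.3%. The stated 90 reproduces. The formula is the one for an unadjusted comparison of two proportions, so plan and test agree.

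**2. Power with stratification.** Trials were simulated with 90 per arm and failure of 26% versus 10%. Assumptions, none given in the documents: 50% nulliparous, 60% with a Bishop score of 3 or less, independent factors, and the same odds ratio (OR) for failure for each factor.

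The stratified test over the four strata k is
z = Σ(y_Ck − m_k n_Ck/N_k) / √Σ[n_Ck n_Tk m_k (N_k − m_k) / (N_k²(N_k − 1))],
where C and T are the misoprostol and combined arms, y is failures in an arm, m is total failures, n is arm size and N is stratum size.

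Results from 40,000 trials per row (Monte Carlo standard error of each power √(0.81 × 0.19/40,000), about 0.2 points):

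| OR per factor | Chi2 | Stratified | Change (points) |
|---|---|---|---|
| 1 | 81.3% | 80.9% | −0.4 |
| 1.5 | 81.5% | 81.4% | −0.1 |
| 2 | 81.0% | 81.7% | +0.7 |
| 3 | 80.9% | 83.4% | +2.5 |
| 5 | 81.2% | 85.8% | +4.6 |

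With no treatment effect, both tests rejected in about 5% of trials in every setting. A separate run of 20,000 trials per setting gave changes of −0.4, +0.6, +2.4 and +4.9 points at ORs of 1, 2, 3 and 5. In that run the Mantel-Haenszel risk-difference interval covered the true value in 94% to 95% of trials.

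**3. Chance imbalance.** For a factor with prevalence p, the between-arm difference has SD √(2p(1 − p)/90).
- p = 0.5: SD 7.5 points; probability of a 10-point gap 2 × [1 − Φ(0.10/0.0745)] = 18%.
- p = 0.6: SD 7.3 points; probability 17%.

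These are normal approximations. Summing the two Binomial(90, p) distributions exactly gives about 20% for a gap of at least 9 women (10 points) and about 15% to 16% for at least 10 women.

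**4. What an imbalance does.** When parity is unbalanced by 9 or more women against the combined arm (about 10% of trials), Chi2 power falls to about 75%, 71% and 68% at ORs of 2, 3 and 5. The stratified test keeps about 82%, 83% and 85%.

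**The case against.** The strongest case against is that nothing here is wrong. A Chi2 test in a randomised trial is valid, holds alpha at 5% with chance imbalance already allowed for, and is the test that the sample size was built on. Covariate adjustment may also appear in an analysis plan that is not shown. All of this stands. What remains is that the protocol itself fixes a comparison, and a better one is available at almost no cost.

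A reader might go further in four ways that the documents do not support.
- **That substantial power is being given away.** The gain rests on assumed odds ratios and is close to nil at ORs up to 2. Entry is also limited to low Bishop scores (below 6 in the inclusion criteria, 6 or less in the earlier *Study population* entry). That narrows the range over which the score can predict.
- **That these are shown to be the strongest predictors.** The protocol lists factors and reports one contrast from a cited study, but gives no effect size. It also names prior vaginal delivery, which overlaps with parity.
- **That both factors are already recorded.** They must be assessed for eligibility, but the protocol does not say that they are entered as data.
- **That imbalance is likely to distort the result badly.** With 18% overall failure and a 50:50 factor, an OR of 3 implies failure rates of 10.3% and 25.7%. A 10-point gap then moves the crude difference by 0.10 × 15.4 = 1.5 points. At an OR of 5 (7.4% and 28.6%) it moves it by 2.1 points. The target difference is 16 points.

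The strata are also thin. Equal strata would hold about 90/4 = 22 women per arm, with about 2 expected failures each in the combined arm. The simulated error rate and interval coverage show that the stratified method copes with this under the assumptions above.

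**Conclusion.** The point holds as a missed efficiency. The stated Chi2 test is sound and consistent with the sample size, but it sets aside prognostic information that the protocol itself describes. Stratifying would change power by about −0.4 to +5 points for assumed odds ratios of 1 to 5, and would guard against an imbalance of 10 points or more that arises in about 17% to 18% of trials for a given factor. These sizes depend on the assumed prevalences, odds ratios and independence of the factors.

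It is not a remedy for the larger problem in *Sample size calculation*. That section first says "We postulate that offering a combined use of misoprostol and Foley catheter will reduce this proportion to 16"% and then uses 10% failure (90% success) in the formula. At 26% versus 16%, 90 per group give 37.6% power and about 260 per group would be needed. Stratification lifts the 37.6% to at most about 43% in these settings. That conflict has to be settled separately.

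**What to change.** Replace the sentence on the comparison of proportions, for the primary outcome, with wording such as:

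*Failed induction will be compared between arms, by intention to treat, with the Cochran-Mantel-Haenszel test (two-sided, 5% level) and the Mantel-Haenszel risk difference with 95% CI, stratified by parity (nulliparous/parous) and baseline Bishop score (3 or less/above 3). An unadjusted Chi2 test will be reported as a supporting analysis.*

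Add parity and Bishop score to the questionnaire, recorded before the envelope is opened. If a separate analysis plan exists, it should say the same. The randomisation procedure need not change.

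**Cost.** Two baseline fields, one or two sentences, slightly more analysis work, and about 0.4 points of power if neither factor turns out to be prognostic. If SPSS version 21, the named package, does not give the risk difference directly, it can be computed from the four 2 × 2 tables as Σw_k d_k / Σw_k, where d_k is the difference in failure proportions in stratum k and w_k = n_Ck n_Tk / N_k.
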